**Figure 2 fig2:**
[figure not shown]
Overall process of the clinical trial.

**Table 1 tab1:** Inspection schedule for cohort 1.

Parameters	Baseline	Bowel preparation	Treatment period						Follow-up
			First dose treatment	Intensive treatment	Maintenance treatment				
Time window	D-21 ~ D-7	D-6 ~ D-1	D1 ~ D7	D8 ~ D28	D29 ~ D42	D43 ~ D56	D57 ~ D71	D71 ~ D84	D85 ~ D169
Informed consent	X								
Inclusion and exclusion criteria	X								
Demographic data^a^	X								
Medical and treatment history	X								
Height	X								
Weight	X							X	X
Vital signs^b^	X							X	X
Allergy history	X								
Health checkup	X							X	X
Routine blood test	X							X	X
Blood biochemistry	X							X	X
Urinalysis	X							X	X
Fecal routine	X							X	X
Fecal sample collection^c^	X			X		X		X	X
Urine sample collection^c^	X			X		X		X	X
Blood sample collection^c^	X							X	X
Bowel preparation		X							
FMT			X						
CARS	X			X		X		X	X
SRS	X			X		X		X	X
GSRS	X			X		X		X	X
ABC	X			X		X		X	X
CSHQ	X			X		X		X	X
PEP3	X			X		X		X	X
rehabilitation training	X								
Acceptance survey^d^			X	X				X	
Diet Record	X								
Adverse event record	X								
Combined medication record	X								

FMT, Fecal Microbiota Transplantation; CARS, Childhood Autism Rating Scale; GSRS, Gastrointestinal Symptom Rating Scale; ABC, Autism Behavior Checklist; PEP3, Psychoeducational Profile(Third Edition); SRS, Social Responsiveness Scale; CSHQ, Children’s Sleep Habits Questionnaire.

1 Demographics: date of birth, age, sex, ethnicity.

2 Vital signs: temperature, blood pressure, heart rate (pulse), respiratory rate.

3 Sample collection:

a Stool sample collection: Stool samples will be collected for macro-genome sequencing and metabolomic analysis during the screening period, every fortnight after the start of treatment for macro-genome sequencing, and every four weeks for metabolomic analysis until the end of the study.

b Urine sample collection: Urine samples will be collected for metabolomic analysis during the screening period and every four weeks from the start of treatment until the end of the study.

c Blood sample collection: Blood samples will be collected for metabolomic analysis during the screening period, at the end of treatment (week 13), and at the end of the study (week 25) for metabolomic analysis and safety data collection in the blood.

d Acceptance questionnaires: Part A and Part B questionnaires will be completed by legal guardians only during the screening period; Part A and Part B questionnaires will be received by subjects and/or legal guardian at the end of the first dose of treatment, booster treatment and maintenance treatment, respectively, (see appendix for details).

##### Cohort 2

2.5.2.2.

After the legal guardian signs the ICF, during the screening period (D-14 to D0), the patient’s demographic information (including date of birth, age, sex, and ethnicity), medical and treatment history, allergy history, vital signs (such as temperature, blood pressure, heart rate, and respiratory rate), physical examination, height and weight measurements, as well as data from routine blood, blood biochemistry, urine and fecal tests will be collected and evaluated to determine the patient’s health status.

After the legal guardian signs the ICF, the screening period (D-14 to D0) will involve collecting demographic data (such as birth date, age, gender, and nationality), important medical history, treatment history, and allergy history of the subjects. Vital signs, including temperature, blood pressure, heart rate, respiratory rate, physical examination, height and weight measurements, as well as data from routine blood, blood biochemistry, urine and fecal tests, will also be recorded to determine the patient’s health status.

During the sampling period (D1 to D7), one stool sample will be collected for macroeconomic and metabolomic analysis, and one urine sample and a blood sample will also be collected for metabolomic analysis (Table 2 and Figure 2), following which they will be eligible for discharge.

**Table 2 tab2:** Inspection schedule for Cohort 2.

Parameters	Baseline	Sample collection period
Time windows	D-14 to D0	D1 to D7
Informed consent	X	
Inclusion and exclusion criteria	X	
demographic data^1^	X	
Medical and treatment history	X	
Vital signs^2^	X	
allergy history	X	
health checkup	X	
routine blood test	X	
Blood biochemistry	X	
Urinalysis	X	
Fecal routine	X	
Fecal sample collection^3^		X
Urine sample collection^3^		X
Blood sample collection^3^		X

1 Demographics: date of birth, age, sex, ethnicity.

2 Vital signs: temperature, blood pressure, heart rate (pulse), respiratory rate.

3 Stool sample collection: Stool samples will be collected for macro-genome sequencing and metabolomic analysis during the screening period.

3 Urine sample collection: Urine samples will be collected for metabolomic analysis during the screening period.

3 Blood sample collection: Blood samples will be collected for metabolomic analysis during the screening period.

### Statistical analysis

2.6.

Bioinformatics and statistical analyses will be conducted by professionals using specialized software tools. Analysis of clinical scale results will involve comparing changes in ABC, CARS, SRS, GSRS, CSHQ and PEP3 scales before and after FMT. Differences in scale results between pre- and post-treatment and control groups will also be assessed. To analyze gut flora and metabolites, we will examine alpha-diversity, beta-diversity, bacterial symbiotic networks, and metabolome analysis using the R language MetaboAnalystR package. This package will enable the quantification of metabolite content and the identification of characteristic metabolites. Mann–Whitney U and Kruskal-Wallis tests will be used to analyze differences in gut flora and metabolites between groups. To explore the correlation between gut flora, metabolites, and improvements in ASD symptoms, gastrointestinal symptoms, and sleep symptoms, we will use Spearman’s correlation test.

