### Study design

2.1.

This is a single-center, double-blind, double-modeled, randomized, interventional clinical study aiming at exploring the efficacy and safety of FMT formulation on an interventional treatment of children with ASD. The degree of improvement in their symptoms will be assessed using several scales. Additionally, changes in the composition and structure of their intestinal flora and metabolites of the flora in their blood, urine and feces before and after treatment will also be assessed by macro-genomic sequencing and metabolomics. The study will also evaluate the differences in the gut flora of children with ASD and healthy children and the acceptability of FMT pediatric preparations by children with ASD and their legal guardians.

The primary endpoint of the study is the change from baseline in Childhood Autism Rating Scale (CARS) scores in children with ASD after 12 and 24 weeks of treatment. The secondary endpoints are the variations in assessment scales, and gut flora and included five main points:

(1) Variations in scores from baseline in the Social Responsiveness Scale (SRS), Autism Behavior Checklist (ABC), Psychoeducational Profile Third Edition (PEP3), Gastrointestinal Symptom Rating Scale (GSRS), and Children’s Sleep Habits Questionnaire (CSHQ) after 12 and 24 weeks of treatment;(2) Variations in gut flora characteristics (including alpha-diversity, flora composition, beta-diversity, colonizing bacteria, differential bacteria, and metabolic pathway function) in children with ASD after treatment compared to baseline and donors;(3) Differences in intestinal flora characteristics (including alpha-diversity, flora composition, beta-diversity, differential bacteria, and metabolic pathway function) between children with ASD (baseline) and healthy children;(4) The incidence of adverse events during the treatment of children with ASD;(5) Variations in the FMT acceptance scale scores for participants with ASD and their legal guardians.

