The patients will be divided into two cohorts: Cohort 1 will include 42 children aged 3–9 years diagnosed with ASD, while Cohort 2 will include 30 healthy children aged 3–9 years. The sex ratio and age range of children enrolled in Cohort 1 and Cohort 2 will be kept roughly the same. In Cohort 1, subjects who meet the entry criteria will undergo a two-week screening visit after the legal guardian signs the informed consent. They will then be randomly allocated to either the trial or control group in a 2:1 ratio. Children in the trial group will undergo rehabilitation and FMT, while the control group will receive rehabilitation and placebo. All children will undergo a 12-week treatment period following the completion of bowel preparation and followed up for 12 weeks, during which they will receive only rehabilitation. A homogenous rehabilitation scheme will be performed on all the ASD children in Cohort 1. The study participants will be discharged at week 25 after the end visit. In Cohort 2, after the legal guardian signs the informed consent, they will undergo a physical examination, assessment of vital signs, and various laboratory examinations within two weeks to confirm their health status. Blood, urine, and fecal samples will be collected within one week, and the children will be discharged. Metabolomics analysis will be performed on blood and urine samples, while macro-genomic sequencing and metabolomics analysis will be conducted on fecal samples.

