### Inclusion/exclusion criteria

2.2.

The study participants in each cohort will meet all inclusion criteria to be eligible for this trial. For cohort 1, the patients will:

(1) have a diagnosis of autism as outlined by a child psychiatrist according to the Diagnostic and Statistical Manual of Mental Disorders (5th edition) and positive results on both the Autism Diagnostic Observation Schedule and Autism Diagnostic Interview-Revised assessments;(2) age 3–9 years, regardless of gender;(3) not have immunodeficiency disorders;(4) provide signed ICF by participants’ legal guardians who fully understand the study;(5) have an ABC score ≥ 62 at the time of screening;(6) meet two of the following scale scores at the time of screening: Childhood Autism Rating Scale (CARS) score ≥ 38; Social Responsiveness Scale (SRS) score ≥ 75.

For cohort 2, the patients will:

(1) age 3–9 years;(2) have a male to female ratio as close to cohort 1 as possible;(3) provide signed ICF by participants’ legal guardians who fully understand the study;(4) have normal physical examination, vital signs and important laboratory test results.

Subjects meeting any of the following exclusion criteria will not be allowed to participate.

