#### Experimental flow

2.5.2.

##### Cohort 1

2.5.2.1.

The study flow for Cohort 1 will be divided into seven phases: screening period, bowel preparation, first treatment dose, intensive treatment, maintenance treatment, follow-up, and exit (Figure 2). The patients will undergo stool and urine sample collection, relevant examinations, and scale assessments (Table 1). During the screening period (D-21 ~ D-7), the eligible ASD patients will be assessed based on the implemented scales and complete all required examinations, and the baseline data will be recorded. In the bowel preparation phase (D-6 ~ D-1), patients in both the trial and control groups will undergo bowel preparation with oral rifaximin suspension or rifaximin mimetic for five days at 0.1 g each time, four times daily, followed by one day of polyethylene glycol bowel cleansing. The first treatment dose (D1 ~ D7) will involve administering a total of approximately 700 mL of the therapeutic drink (containing 66 mL of bacterial liquid or placebo) orally over 3 to 5 consecutive days of the week, depending on the subject’s acceptance of the therapeutic drink and the volume available for each dose. Intensive treatment (D8 ~ D28) will involve an intensive dose of approximately 60 mL of the treatment drink (containing 6 mL of bacterial fluid or placebo) once a week for 3 weeks. During the maintenance treatment phase (D29 ~ D84), once weekly doses of approximately 10 mL of the treatment drink (containing 0.6 mL of bacterial liquid or placebo) will be administered for 8 weeks. During the follow-up period (D85 ~ D169), the subjects will receive the same rehabilitation as during the treatment period. They will be discharged at week 25 after completion of the end-visit examination (D170). Throughout the treatment period, they will be asked to adhere to the “Dietary Manual for People with Autism Receiving FMT Therapy” as closely as possible, with a legal guardian completing a weekly dietary record form.

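### The scale analysis names before-after change under FMT first, and nowhere makes the randomised FMT-versus-placebo difference in CARS change the decisive comparison

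*Protocol article*

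**What the plan says.** Section 2.6 (Statistical analysis) gives two sentences to the clinical scales. The first reads: "Analysis of clinical scale results will involve comparing changes in ABC, CARS, SRS, GSRS, CSHQ and PEP3 scales before and after FMT". The second adds: "Differences in scale results between pre- and post-treatment and control groups will also be assessed". No test, model or decisive contrast is named for the scales; the tests named later in the section concern flora, metabolites and correlations.

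Section 2.1 (Study design) words the primary endpoint in the same within-child way: "The primary endpoint of the study is the change from baseline in Childhood Autism Rating Scale (CARS) scores in children with ASD", at 12 and 24 weeks. It mentions no comparison between arms. Section 2.3 (Sample size estimation) points the other way: the 42 children (28 FMT, 14 placebo) are meant to show an effect on CARS relative to placebo. Yet the only effect it states is a 5-point mean reduction in the FMT group, with no placebo change.

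Three further statements matter:

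- **Entry thresholds (section 2.2).** Children must "have an ABC score ≥ 62 at the time of screening" and must meet two of these: "Childhood Autism Rating Scale (CARS) score ≥ 38; Social Responsiveness Scale (SRS) score ≥ 75". Only two are listed, so as written both apply.
- **Baseline (section 2.5.2.1).** In the screening window, D-21 to D-7, "the eligible ASD patients will be assessed based on the implemented scales and complete all required examinations, and the baseline data will be recorded". Table 1 has one pre-treatment column for the scales and no later baseline measurement.
- **Background treatment (section 2.1).** "Children in the trial group will undergo rehabilitation and FMT, while the control group will receive rehabilitation and placebo".

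**The concern.** In a randomised, placebo-controlled trial the evidence for efficacy is the difference between arms. Here the endpoint wording, the stated effect and the first-named analysis are all framed within the FMT arm. If the FMT arm falls significantly and the difference from placebo is not significant, the text does not say which result governs.

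The within-arm result is easy to obtain without any FMT effect. On CARS, ABC and SRS, children are selected for high scores and then compared with those same scores, so some fall is expected from regression to the mean. On all six scales, rehabilitation and the development of children aged 3 to 9 add further change. Randomisation balances these influences between the arms, but a before-after test counts them as FMT benefit.

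**Working it through.** **The plan's own figure.** The total of 42 can be neither confirmed nor refuted, because section 2.3 gives no SD and no placebo change. It can be solved backwards. With 15% dropout, 28 × 0.85 ≈ 24 and 14 × 0.85 ≈ 12 children are evaluable. For a 5-point difference between arms (placebo change taken as 0), one-sided 5% and 80% power:

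SD = 5 / [(1.645 + 0.842) × √(1/24 + 1/12)] = 5.69 (normal approximation), or 5.57 with the t distribution.

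An SD of 5.5 gives 36 evaluable children, and 36/0.85 = 42.4, so 43, close to the stated 42. I use 5.6 below as an assumed SD of change; it is not a figure from the article.

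**Possible regression to the mean on CARS.** For a normal source population cut at 38:

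expected fall = (1 − reliability) × SD × λ, with z = (38 − mean)/SD and λ = φ(z)/[1 − Φ(z)].

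Assumed inputs: mean 34 to 38, SD 5 to 6, reliability 0.7 to 0.9.

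- Low end (mean 38, SD 5, reliability 0.9): 0.1 × 5 × 0.798 = 0.40 points.
- High end (mean 34, SD 6, reliability 0.7): 0.3 × 6 × 1.265 = 2.28 points.

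**Chance that a before-after test is positive with no FMT effect.** One-sample t test, n = 24, one-sided 5%, non-centrality = fall × √24 / 5.6:

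| Fall shared by both arms | Non-centrality | Probability positive |
|---|---|---|
| 0.4 | 0.35 | 0.10 |
| 1 | 0.88 | 0.21 |
| 2 | 1.75 | 0.52 |

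A 3-point fall gives 0.82, but that exceeds the regression range above and would need a contribution from rehabilitation or maturation as well.

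**Why the two comparisons may disagree.** With 24:12 evaluable and SD 5.69, power between arms is 0.80 only if placebo does not change. If FMT falls 5 points and placebo falls 1 or 2, the true difference is 4 or 3 and power is 0.63 or 0.44.

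**What baseline adjustment gains over a comparison of change scores.** Let r be the correlation of baseline with follow-up in the source population, and d the factor by which selection at CARS ≥ 38 shrinks the baseline variance, d = 1 + zλ − λ². Then

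variance ratio, ANCOVA to change score = (1 + r) / [(1 + r) + (1 − r)d].

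- Equal variances (d = 1): the ratio is (1 + r)/2, that is 0.85 at r = 0.7 and 0.75 at r = 0.5, a cut of 15% to 25%.
- Truncated baseline with the assumed means and SDs: d is 0.22 to 0.36. The smallest cut is at r = 0.7, d = 0.22: 1.7/1.767 = 0.96, about 4%. The largest is at r = 0.5, d = 0.36: 1.5/1.68 = 0.89, about 11%.

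**The case against.** A reader might infer that the before-after test replaces the placebo comparison, or is the primary analysis. The article does not support either reading. The second sentence on the scales does plan a comparison with control; its wording is loose, but it is most naturally read as comparing change with the control group. Section 2.3 sizes the trial against placebo, and the arms are randomised, blinded and given the same rehabilitation. Order of mention is not a hierarchy, and no alpha or efficacy claim is attached to the before-after test.

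A reader might also infer that the between-arm analysis is unadjusted. The article names no model, adjusted or not, and a condensed article may leave that choice to the full protocol or SAP. The missing covariate is therefore not an error in itself.

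Two further limits stand. Only CARS, ABC and SRS have entry thresholds, so regression to the mean through selection does not apply in this way to GSRS, CSHQ and PEP3. In the randomised comparison, regression to the mean, rehabilitation and maturation are expected to cancel. All the magnitudes rest on assumed inputs.

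What the objection leaves intact is that an uncontrolled comparison is stated first for the primary scale, and that no statement makes the randomised contrast decisive.

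**Conclusion.** The concern holds as a failure to fix which comparison decides efficacy. It does not hold as a claim that the placebo comparison is missing. Sections 2.1 and 2.6 leave room to claim efficacy from a within-arm fall, and for CARS, ABC and SRS the entry rule and the choice of baseline make such a fall particularly likely.

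In the illustration, the chance of a positive before-after test without any FMT effect is about 10% to 52% for shared falls of 0.4 to 2 points, against a nominal 5%. This depends on the assumed SD of change of 5.6, on 24 evaluable FMT children, and on the assumed size of the fall. The direction of the problem does not depend on these values.

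The precision gained by baseline adjustment is a modest extra: about 4% to 11% lower variance than change scores once the baseline is truncated at CARS ≥ 38, and 15% to 25% only if baseline and follow-up variances are equal. It supports the remedy but is not the reason for it.

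**What to change.** Add to section 2.6, or to the SAP before unblinding:

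1. Efficacy is judged on the FMT-minus-placebo difference in CARS, in all randomised children. It is estimated by ANCOVA with baseline CARS as covariate, or by a repeated-measures model with that covariate using the CARS visits already in Table 1, and reported with a confidence interval.
2. The secondary scales use the same model, each with its own baseline as covariate.
3. Before-after tests within an arm are descriptive and are not a basis for claiming efficacy.

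The primary endpoint in section 2.1 should be reworded to name the contrast between arms. The cost is a few lines of text; no new data, visits or children are needed.

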## Risk prevention and management

3.

A randomized, double-blind study with *N* = 52 patients suffering from irritable bowel syndrome evaluated the safety and efficacy of oral FMT capsules. It revealed that diarrhea was the only statistically significant adverse event, and no serious adverse events (SAEs) were observed (Halkjaer et al., 2018). Other FMT-related studies found that nausea and diarrhea were the most common adverse events associated with oral FMT capsules. However, these symptoms are generally self-alleviating and do not require treatment. When completing the adverse event form, all relevant information will be collected, including the adverse event and associated symptoms, time of occurrence, severity, duration, correlation with the bacterial liquid/placebo, action taken, and final outcome. The supervisor will confirm that the adverse events are reported within the specified period in accordance with relevant laws and regulations, the trial protocol, ethics committee, and sponsor’s requirements. In the event of an adverse event, the investigator will closely observe the subject. In the case of SAEs, subsequent FMT will be immediately discontinued.

If a severe allergic reaction occurs, standard anti-allergy measures will be taken, and medication will be administered if there are no contraindications.If an inflammatory bowel disease attack occurs, standard treatment measures for inflammatory bowel disease attacks should be taken, including stool and blood sample collection. Traceability testing and analysis should be initiated immediately to determine the cause of the attack.In the event of a severe infection, blood cultures and stool tests will be performed immediately to identify the causative organism and the most effective antimicrobial agent. Broad-spectrum antibacterial drugs and supportive therapy will be administered while awaiting test results, which may help to boost the patient’s resistance.If a serious infection or any other emergency related to the FMT intervention occurs during the trial, immediate action will be taken. Blood and stool samples will be collected from the subject for pathogen detection and analysis to trace the source of the causative pathogen before administering any antimicrobial agent

## Ethics and dissemination

4.

This study has been approved by the Ethics Committee of Shanghai Sixth People’s Hospital in December 2021 and registered with the China Clinical Trials Center (registration number: ChiCTR2200058459). The investigator will explain the study’s background, pharmacological characteristics of the study drug, trial protocol, and potential benefits and risks of participating in the trial to each subject’s legal guardian and obtain written informed consent before enrolling the subject. Good Clinical Practice and International Council for Harmonization of Technical Requirements for Pharmaceuticals for Human Use guidelines will be followed by the investigator and all participants. A dedicated team, independent of the Clinical Research Center project team, will manage and monitor the study. Participating subjects will be legally covered by insurance. The study’s results will be published in medical journals or conferences, while the subjects’ information will be kept confidential as required by law. The subjects’ personal information will not be disclosed except as mandated by relevant laws. Patient information will be accessed by government authorities and hospital ethics committees when required.

